### Risks associated with radiation exposure:

A chest-x ray will be performed if there is not an available film that has been performed in the last 3 months. The maximum radiation dose for one chest x-ray is 0.04 mSv, which is equivalent to 5 days of natural background radiation.

**Known Potential Benefits:**

Volunteers will not benefit directly from participation in this study. However, it is hoped that the information gained from this study will contribute to the development of a safe and effective TB vaccine for HIV negative and positive individuals. The only benefits for participants would be information about their general health status.

## **2 OBJECTIVES**

### **Primary:**

To assess the safety of two intradermal injections of  $1 \times 10^8$  pfu MVA85A, when administered to healthy subjects who are infected with HIV.

### **Secondary:**

To assess the immune responses induced by two vaccinations with MVA85A in healthy subjects who are infected with HIV, including the boosting affect of second MVA85A vaccination

To compare the immune response between subjects who are and who are not on ARVs after vaccination with MVA85A

### **Endpoints:**

The specific endpoints for safety and reactogenicity will be actively and passively collected data on adverse events (AEs). The specific endpoints for immunogenicity will be markers of cell-mediated immunity.

### **3 STUDY DESIGN**

This is an open label Phase I safety study of two intradermal injections of  $1 \times 10^8$  pfu MVA85A, when administered to healthy subjects who are infected with HIV.

#### **Sample size:**

This is an observational and descriptive safety study, 24 subjects will be recruited from HIV clinics and vaccinated with MVA85A. Half of the subjects will not have started on ARVs and half will be stable on ARVs. This sample size should allow determination of the magnitude of the outcome measures, especially of serious and severe adverse events, rather than aiming to obtain statistical significance.

#### **End of trial:**

The trial ends when the last volunteer has completed their last (twelve month) follow-up visit.

## 4 STUDY POPULATION

All subjects must meet all of the inclusion criteria to participate in this study.

### **Inclusion Criteria**

- Healthy adults aged 18 to 50 years
- Resident in or near Dakar for the duration of the study
- Willingness to allow the investigators to discuss the volunteer's medical history with the volunteer's HIV lead physician
- Willing to use effective contraception throughout duration of study (if female)
- Written informed consent

### **Group 1 (HIV infected not on ARV):**

- HIV antibody positive; diagnosed at least 6 months previously
- CD4 count >300 and CD4 count nadir 300
- HIV viral load not >100,000 copies per millilitre

### **Group 2 (HIV infected on ARV):**

- HIV antibody positive; diagnosed at least 12 months previously
- Two CD4 counts prior to enrolment >300; and CD4 count nadir 100
- Stable on same ARV regimen for at least 12 months
- Undetectable HIV viral load for at least 12 months

### **Exclusion Criteria**

- Any clinically significant abnormal finding on screening biochemistry or haematology blood tests or on urinalysis
- Previous history of TB disease and/or treatment
- Any AIDS defining illness
- CXR showing TB or evidence of other active infection
- Prior receipt of a recombinant MVA or Fowlpox vaccine
- Use of any investigational or non-registered drug, live vaccine or medical device other than the study vaccine within 30 days preceding dosing of study vaccine, or planned use during the study period
- Administration of chronic (defined as more than 14 days) immunosuppressive drugs or other immune modifying drugs within six months of vaccination. (For corticosteroids, this will mean prednisolone, or equivalent,  $\geq 0.5$  mg/kg/day. Inhaled and topical steroids are allowed.)
- History of allergic disease or reactions likely to be exacerbated by any component of the vaccine, e.g. egg products
- Presence of any underlying disease that compromises the diagnosis and evaluation of response to the vaccine (including evidence of cardiovascular disease, history of cancer (except basal cell carcinoma of the skin and cervical carcinoma in situ), history of insulin requiring diabetes mellitus, any ongoing chronic illness requiring ongoing specialist supervision (e.g., gastrointestinal), and chronic or active neurological disease)

- History of  $\geq 2$  hospitalisations for invasive bacterial infections (pneumonia, meningitis)
- Suspected or known current drug and/or alcohol abuse
- Seropositive for hepatitis B surface antigen (HBsAg) and/ or hepatitis C (antibodies to HCV)
- Evidence of serious psychiatric condition
- Any other on-going chronic illness requiring hospital specialist supervision
- Any confirmed or suspected immunosuppressive or immunodeficient condition, **other than** HIV infection, such as asplenia
- Evidence of hepatomegaly
- Administration of immunoglobulins and/or any blood products within the three months preceding the planned administration of the vaccine candidate
- Pregnant/lactating female and any female who is willing or intends to become pregnant during the study
- Any history of anaphylaxis in reaction to vaccination
- PI assessment of lack of willingness to participate and comply with all requirements of the protocol, or identification of any factor felt to significantly increase the participant's risk of suffering an adverse outcome

**Group 1 (HIV infected not on ARV):**

- Current CD4 count less than 300 or CD4 count nadir less than 300
- Any ARV therapy within the last six months

**Group 2 (HIV infected on ARV):**

- CD4 count less than 300 or CD4 count nadir less than 100
- Detectable HIV viral load at  $>75$  copies/ml

**Recruitment Procedures**

Patients will be screened from the Fann Teaching Hospital Ambulatory Treatment Centre (CTA)

**Screening visit**

The screening will take place at the Centre Régional de Recherche Clinique et de Formation at the Fann Teaching hospital which is in front of the CTA (less than 100 metres). The information sheet will be made available to the volunteer at least 24 hours prior to the screening visit. The screening visit may take place up to 90 days prior to vaccination. At the screening visit, before screening is undertaken, the screening process will be reviewed in detail with each prospective volunteer and all questions about the screening process answered. Each potential subject will be fully informed so that they understand the following general principles:

- Participation in the study is entirely voluntary
- Refusal to participate involves no penalty or loss of medical benefits
- The subject may withdraw from the study at any time

- The subject is free to ask questions at any time to allow him or her to understand the purpose of the study and the procedures involved
- The study involves research of an investigational vaccine
- There is no direct benefit for participating

The aims of the study and all tests to be carried out will be explained by the investigator. Written informed consent will be obtained. Potential subjects will be informed that there may be leftover samples of their blood (after all testing for this study is completed), and that such samples may be stored up to a maximum of 15 years for possible future research (exploratory immunology assays). Subjects will be able to decide if they will permit such future use of any leftover samples. If a subject elects not to permit this, all of that subject's leftover samples will be discarded after the required period of storage to meet Good Clinical Practice (GCP) and regulatory requirements.

**Events at screening:**

- A baseline medical history and physical examination will be performed
- Inclusion and exclusion criteria will be checked using a tabulated format
- Vital signs will be checked
- Subjects will be counselled by one of the investigators for Hepatitis B and Hepatitis C testing
- Blood will be drawn for HIV, HBV and HCV testing, haematology, biochemistry, viral load and CD4 cell count, typing for HLA variants, other genetic variants that may be relevant to the immune response to vaccines, and exploratory immunological assays. A serum  $\beta$ HCG test will be done on women to test for pregnancy.
- Urinalysis, to exclude glycosuria and significant proteinuria will be performed
- A chest-x ray will be performed if there is not an available film that has been performed in the last 3 months.
- 1 week after screening, volunteers will attend to obtain their results.

All documents and procedures will be in French, having been translated and backtranslated from English. Wolof translators will be present when necessary.

## 5 STUDY ENROLLMENT AND SCHEDULE OF FOLLOW-UP VISITS

Subjects who match all inclusion and exclusion criteria and who are available for the follow up will be invited to take part after screening. Subjects will attend the Bacteriology and Virology Laboratory at Le Dantec Teaching Hospital for vaccination. All volunteers will be vaccinated with MVA85A and will not be randomised.

The following table illustrates the sequence of events from screening, through vaccination (day 0) and subsequent follow-up visits (explained in more detail in the text that follows):

**Table 2: Illustration of sequential events (screening and subsequent follow-up):**

| Visit number              | 1         | 2              | 3–8 | 9   | 10  | 11  | 12             | 12.1 ^ | 13–18            | 19  | 20  | 21  | 22  |
|---------------------------|-----------|----------------|-----|-----|-----|-----|----------------|-------------------|------------------|-----|-----|-----|-----|
| Day                       | Screening | 0              | 1–6 | 7   | 28  | 84  | 168
(+/-14) | 168-350           | 1–6 ◇ | 7   | 28  | 84  | 168 |
| Medical history           | √         | (√)            | (√) | (√) | (√) | (√) | (√)            | (√)               | (√)              | (√) | (√) | (√) | (√) |
| Physical examination      | √         | (√)            | (√) | (√) | (√) | (√) | (√)            | (√)               | (√)              | (√) | (√) | (√) | (√) |
| Vital signs °  | √         | √              | √   | √   | √   | √   | √              | √                 | √                | √   | √   | √   | √   |
| Urinalysis                | √         | √ † |     |     |     |     | √ † | √ †    |                  |     |     |     |     |
| Chest x-ray #  | √         |                |     |     |     |     |                |                   |                  |     |     |     |     |
| Venepuncture              | √*        | √*             |     | √*  | √*  | √*  | √*             | √*                |                  | √*  | √*  | √*  | √*  |
| Vaccination               |           | √              |     |     |     |     | √              | √                 |                  |     |     |     |     |
| Injection site inspection |           | √              | √   | √   | √   | √   | √              | √                 | √                | √   | √   | √   | √   |
| Adverse events documented |           | √              | √   | √   | √   | √   | √              | √                 | √                | √   | √   | √   | √   |

(√) If considered necessary (emphasizing any acute complaints)

^ Visit 12.1 is only required if a subject has been for their 6 month visit but was not revaccinated because the 6 month visit was prior to the second vaccination amendment

° Temperature (°C), blood pressure (mmHg), pulse rate (beats/minute)

† Women only for pregnancy test

# Performed if no available CXR within the last 3 months

\* See table 3 for exact blood tests performed at each visit

◇ Note that the days from this point on are shown as days after the second vaccination

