The second possible way to enhance the immunogenicity in this group is to include a second MVA85A booster vaccine. In the first trial we conducted with MVA85A, we administered two doses of MVA85A, three weeks apart [37]. In this study we saw no impact of the second MVA85A immunization, and at such a short interval between doses, this is likely to be due to anti-vector immunity. Other studies using a recombinant MVA expressing malaria antigens have shown that boosting with the same vaccine one year after first dose is highly effective [31]. We would therefore like to boost subjects in this study in both the ARV and no ARV group with a second MVA85A immunization, administered ~6-12 months after primary immunization. Subjects already recruited into the first (no ARV) arm will be contacted, informed of the results so far and asked if they would be happy to receive a second immunization. They are clearly under no obligation to do so and this will be clearly explained to them. Subjects in the second (ARV) arm of this study will be consented to receive two immunisations with MVA85A, with ~6-12 months between the two doses. It is thought that by boosting ~6-12 months after the first vaccination that the anti-vector immunity will have waned and should not impact the potential boosting by the second MVA85A vaccination.

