**Contraindications to Vaccination**

The following adverse events constitute contraindications to administration of vaccine at that point in time; if any one of these adverse events occurs at the time scheduled for vaccination, the subject may be vaccinated at a later date, or withdrawn at the discretion of the investigator. The subject must be followed until resolution of the event as with any adverse event.

- Acute disease at the time of vaccination. (Acute disease is defined as the presence of a moderate or severe illness with or without fever.) All vaccines can be administered to persons with a minor illness such as diarrhoea, mild upper respiratory infection with or without low-grade febrile illness, i.e., temperature of  $<37.5^{\circ}\text{C}$ ).
- Temperature of  $\geq 37.5^{\circ}\text{C}$  at the time of vaccination

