**Subsequent follow-up visits**

Volunteers will be reviewed at 28 (+/- 4 days), 84 (+/- 7 days) and 168 days (+/- 14 days) after vaccination.

- An interim history will be taken and, if considered necessary a physical examination emphasizing any acute complaints will be performed.
- Vital signs will be checked and documented
- The injection site will be inspected and the largest diameter of any hardness or redness present, as well as the degree of pain reported for the time of the visit will be documented into the CRF.
- Solicited adverse events (local and general) that may have occurred since the volunteer was seen on day 7 post vaccination will be documented in the CRF
- Approximately 32-42 ml of blood will be collected for exploratory immunology, viral load and CD4 cell count on day 28, 84 and 168. On day 84 only, haematology and biochemistry will also be performed; therefore, the blood volume will be 40-50 ml.
- On Day 28, HLA typing will be done; therefore, the total blood volume will be 36-46.

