**Booster vaccination:**

- For Group 1, if Day 168 visit is before Protocol 2.0 amendment, the second vaccination will be given between days 168-350 (visit 12.1). However, before the subject receives the second vaccination, all inclusion and exclusion criteria except number 5 (Prior receipt of a recombinant MVA or Fowlpox vaccine) will be reviewed to check if the subject is still eligible to receive the vaccine. At this additional visit, 20 ml of blood will be collected to perform FBC, Biochemistry, CD4 and VL tests. Urinalysis, to exclude glycosuria and significant proteinuria will be performed. If any exclusion criterion are met except number 5, the subject will not be revaccinated.
- For Group 2, the second vaccination will be given at Day 168 (+/- 14 days)
- A photograph of the vaccination site will be taken after revaccination. The subject will only be identifiable by a unique study number.

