**Subsequent follow-up visits**

Volunteers will be reviewed at 28 (+/- 4 days), 84 (+/- 7 days) and 168 days (+/- 14 days) after the second vaccination.

- An interim history will be taken and, if considered necessary a physical examination emphasizing any acute complaints will be performed.
- Vital signs will be checked and documented
- The injection site will be inspected and the largest diameter of any hardness or redness present, as well as the degree of pain reported for the time of the visit will be documented into the CRF.
- Solicited adverse events (local and general) that may have occurred since the volunteer was seen on day 7 post second vaccination will be documented in the CRF.
- Approximately 32-42 ml of blood will be collected for exploratory immunology, viral load and CD4 cell count on days 28, 84 and 168 after the second vaccination. On day 84 after the second vaccination only, haematology and biochemistry will also be performed; therefore, the blood volume will be 40-50 ml.

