#### **4. DEFINITE:**

- Reasonable temporal relationship to study product; and
- Event not readily produced by clinical state, environment, or other interventions; and
- Known pattern of response seen with other vaccines

Every AE observed or reported from the day of injection [Day 0] through to the end of the trial (twelve months after injection) will be recorded on the CRF.

All AEs will be followed until resolution of the symptom or laboratory change occurs, or until a non-study related causality is assigned.

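### Every visit after Day 168 or visit 12.1 is dated from the second injection, so subjects who do not receive it have no scheduled safety visits or bloods for the rest of the twelve-month adverse event period

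*Protocol*

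**What the plan says.** **Schedule.** After the first injection, "Volunteers will be reviewed at 28 (+/- 4 days), 84 (+/- 7 days) and 168 days (+/- 14 days) after vaccination". The second injection is due at Day 168 (+/- 14 days). For Group 1 subjects whose Day 168 visit came before the amendment, section 5 (Booster vaccination) states that "the second vaccination will be given between days 168-350 (visit 12.1"). From there on, the footnote to Tables 2 and 3 applies: "Note that the days from this point on are shown as days after the second vaccination". The text agrees: "Volunteers will be reviewed at 28 (+/- 4 days), 84 (+/- 7 days) and 168 days (+/- 14 days) after the second vaccination". Visits 13 to 22 therefore have no date unless dose 2 is given.

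**Routes to one dose only.**
- Section 1 (Rationale), on asking Group 1 subjects already recruited to accept a second injection: "They are clearly under no obligation to do so and this will be clearly explained to them".
- Section 5 (Booster vaccination), on the visit 12.1 re-check, written for Group 1: "If any exclusion criterion are met except number 5, the subject will not be revaccinated".
- Section 5 (Contraindications to Vaccination), on acute illness or fever on the day: "the subject may be vaccinated at a later date, or withdrawn at the discretion of the investigator".

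**Follow-up promised without reference to dose 2.** Section 8 (Adverse Events Assessment) covers "Every AE observed or reported from the day of injection [Day 0] through to the end of the trial (twelve months after injection"). Section 3 (End of trial) refers to a twelve-month follow-up visit as each volunteer's last. Section 1 (HIV specific risks) promises regular CD4 and viral load monitoring.

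**The concern.** The primary objective is safety, in an uncontrolled trial of 24 subjects. Section 1 names a viral load rise as a hypothetical vaccine risk and plans CD4 and viral load monitoring. For Group 1, a CD4 count below 300 is an exclusion criterion, and so is a clinically significant laboratory abnormality for everyone. At visit 12.1 such a finding both bars dose 2 and, because of how the schedule is dated, removes the subject from every later scheduled draw. The later course of a change that might be a late effect of dose 1 is then not measured on schedule. The late CD4, viral load and laboratory summaries would describe only subjects who remained eligible. No analysis can recover draws that were never scheduled.

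**Working it through.** The protocol gives no figure to reproduce here: the sample size is descriptive, and no number of one-dose subjects is stated. The check is calendar arithmetic on Tables 2 and 3, taking twelve months as 365 days from the first injection.

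**1. Two doses, second at Day 168.** Last visit = 168 + 168 = Day 336. With both +/- 14-day windows the range is 154 + 154 = 308 to 182 + 182 = 364. Time to Day 365 without a visit = 365 - 336 = 29 days.

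**2. Two doses, second at visit 12.1.** Last visit = 168 + 168 = Day 336 up to 350 + 168 = Day 518, before the final window.

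**3. No second dose, last seen at Day 168.**
- Uncovered time = 365 - 168 = 197 days; 197/365 = 54%.
- With the window: 365 - 182 = 183 to 365 - 154 = 211 days.
- Loss relative to the two-dose schedule in step 1 = 197 - 29 = 168 days.

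**4. No second dose, stopped at visit 12.1.** Uncovered time = 365 minus the day of the visit: 365 - 350 = 15 days to 365 - 168 = 197 days.

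**5. Assessments without a date.** Visits 13 to 22 are ten visits. Seven of them (13 to 19, Days 1 to 7 after dose 2) chiefly check reactions to dose 2 and have little purpose without it. The relevant loss is the three later visits (Days 28, 84 and 168 after dose 2). Counting the Day 7 draws as well, Table 3 has four CD4 and viral load draws (Days 7, 28, 84, 168) and two blood count and biochemistry draws (Days 7, 84) after dose 2.

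**6. Share of the trial.** The number of one-dose subjects, k, is not given, so it is assumed. If each stops at Day 168, the share of planned follow-up lost is 168k/(24 x 336):

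| k (assumed) | Share lost |
|---|---|
| 1 | 168/8064 = 2.1% |
| 4 | 672/8064 = 8.3% |
| 6 | 1008/8064 = 12.5% |

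Within a group of 12, each such subject is 1/12 = 8.3% of the group.

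**7. Which injection starts the twelve months.** Section 8 does not say. If the period ran from the second injection, it would have no start date for a one-dose subject. For a two-dose subject it would extend 365 - 168 = 197 days beyond the last scheduled visit.

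**The case against.** A reader might infer that safety follow-up as a whole ends for these subjects. The text does not support that. Section 8 records reported as well as observed events, and follows all events until they resolve or a non-study cause is assigned. Section 5 requires a contraindicating event to be followed to resolution, and section 8 follows any pregnancy to its outcome. None of this depends on dose 2. The safety endpoint explicitly includes passively collected events, so an event can be recorded without a numbered visit. Visit 12.1 itself includes CD4, viral load, blood count, biochemistry and adverse event documentation, so a change present on that day is in the data.

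A reader might also infer that everyone who stops at one dose does so because their health changed. That is not shown. Group 1 subjects may decline for any reason. The re-check covers all criteria except number 5, including residence, pregnancy and use of other investigational products. It is written only for Group 1 at visit 12.1. The contraindication rule sits next to the Day 0 text, offers later vaccination first, and is applied to dose 2 by reading it as covering any scheduled vaccination.

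All of this stands and limits the point to scheduled active assessment. It does not close the gap. A CD4 or viral load shift that begins after the last visit causes no symptom to report and has no scheduled draw to reveal it. The laboratory studies that section 8 lists for monitoring do not include either measure. Follow-up of an open event may stop once a non-study cause is assigned, and section 1 itself warns of natural fluctuation in these markers.

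**Conclusion.** The protocol promises a twelve-month adverse event period, a twelve-month visit and regular CD4 and viral load monitoring, and gives subjects without dose 2 no visit at which to deliver them. The uncovered time is about 197 of 365 days after a Day 168 stop (183 to 211 with the window) and 15 to 197 days after a visit 12.1 stop. These figures assume that the period runs from the first injection.

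For subjects barred or withdrawn for health reasons the loss is related to outcome, and the later scheduled CD4, viral load and laboratory data then come only from subjects who remained eligible. The size of any resulting bias cannot be calculated: neither the number of such subjects nor their later course is known. The 2.1% to 12.5% of planned follow-up shown in the working rests entirely on assuming 1 to 6 one-dose subjects, all stopped at Day 168. Visit schedules belong in the protocol, so this is not something to leave to an analysis plan. It should be corrected.

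**What to change.** Reconcile section 3 (End of trial), section 5 (Contraindications to Vaccination, Booster vaccination, Tables 2 and 3) and section 8 (Adverse Events Assessment) as follows.

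- State that a subject who does not receive the second injection, for whatever reason, stays in the study unless consent is withdrawn.
- Give that subject the remaining safety visits (adverse events, CD4, viral load, blood count, biochemistry) dated from the first injection, including one at the end of the twelve-month adverse event period. Omit any date already passed when dose 2 is ruled out; this matters because visit 12.1 may fall as late as Day 350.
- Distinguish not giving the second injection from withdrawal from the study.
- Say which injection starts the twelve months.

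The rules on who may receive the second injection are untouched. The cost is amendment wording, a footnote or row in Tables 2 and 3, and one or two dated visits per one-dose subject, fewer than the ten already planned for that subject after dose 2.
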